### Interventions

#### Overview

All participants will receive acupuncture based on the Jing Bie theory or conventional acupuncture at a frequency of 3 times a week. To ensure the accuracy and consistency of the treatment administered, all acupuncture physicians participating in this study are required to have passed the clinical standard operation training in this subject and have the corresponding professional qualifications. Moreover, any possible adverse reactions during the study will be recorded in detail.

During the study period, the use of any prescription or nonprescription drugs for insomnia will be prohibited in principle. Participants who are required to use drugs for other diseases, which may affect the central nervous system, or have a severe insomnia problem will be processed and recorded as a “significant program deviation” or “withdrawal from the study” event. For those who do need medication, their complete medication information will be included in the subsequent statistical analysis as a key covariate. All participants are required to maintain a relatively stable work and rest schedule during the study period and to record information such as their bedtime, wake-up time, and occurrence of night awakening in a daily sleep diary. The researchers will review the diary every week to identify and guide individuals who experience excessive daytime sleepiness (>1 h) or significant changes in work and rest schedule (>2 h). Such behavioral changes will be included as covariates in the analysis.

#### Acupuncture Group

This group will include 48 patients. The patients will be placed in a supine position. Acupuncture will be performed bilaterally at Tianrong (SI17) points, with the needle inserted backward obliquely at 45±5° to a depth of 1.0 to 1.5 inches, reinforcing and reducing horizontally, and the needle insertion will be stopped when the patient feels a heat sensation in the auricle.

Acupuncture will be performed bilaterally at Tianyou (TE16) points, with the needle pointing toward the tip of the nose. The needle will be inserted to a depth of 0.5 to 1.0 inch using flat reinforcing and reducing maneuvers, until the sense of soreness and distension obviously stops; the needle will be retained for 30 minutes. The location of acupuncture points is shown in Table 2.

**Table 2. T2:** Acupoint selection and stimulation parameters for the acupuncture group.

Acupoint	Location	Manipulation
Tianyou (TE16)	On the lateral side of the neck, located in the depression at the posterior border of the sternocleidomastoid muscle, level with the mandibular angle.	The needle is directed toward the tip of the nose, the insertion depth is 0.5‐1.0 inch, the reinforcing and reducing maneuvers are flat, needle insertion is stopped when soreness is obvious, and the needle is retained for 30 min.
Tianrong (SI17)	In the lateral aspect of the neck and in the depression on the anterior border of the sternocleidomastoid muscle and posterior to the mandibular angle	The needle is inserted backward obliquely at 45±5° to a depth of 1.0‐1.5 inches, with reinforcing and reducing maneuvers, and needle insertion is stopped when the patient feels a heat sensation in the auricle.

#### Control Group

This group will include 48 patients. The patients will be placed in a supine position. Acupuncture will be performed at Baihui (DU20), Sishencong (EX-HN1), bilateral Qimen (LR13), Zhangmen (LR14), Hegu (LR14), and Taichong (LR3), with reinforcing and reducing maneuvers. The needle insertion will be stopped when acid swelling is obvious, and the needle will be retained for 30 min. The location of acupuncture points is shown in Textbox 2.

Textbox 2.Acupoint selection and stimulation parameters for the control group.
**Acupoints and location**
Baihui (DU20): on the head, 5 inches straight up the hairline or the midpoint of the line between the 2 ear tipsSishencong (EX-HN1): on the top of the head, a total of 4 points located 1 inch anterior, posterior, and bilateral to the BaihuiQimen (LR13): on the chest, in the sixth intercostal space, approximately 4 inches lateral to the anterior median line (midline) and level with the nipple.Zhangmen (LR14): on the lateral abdomen, below the free extremity of the 11th ribHegu (LI4): on the dorsum of the hand, between the first and second metacarpals, at the midpoint of the radial side of the second metacarpalTaichong (LR3): on the dorsal side of the foot, in the posterior depression of the first metatarsal space
**Manipulation**
Tonifying and reducing, until the soreness and distension obviously stops; the needle is retained for 30 minutes

#### Healthy Group

This group will include 48 healthy volunteers without sleep disorders, who will not undergo any treatment.

### Outcome Measures

#### Primary Outcome Measures

##### Sleep Quality Assessed Using the Pittsburgh Sleep Quality Index

The patients will be assessed using the Chinese version of the Pittsburgh Sleep Quality Index (PSQI) questionnaire at each observation point, and the clinical efficacy will be assessed. The questionnaire consists of 19 self-evaluation items and 5 other evaluation items. Only the 19 self-evaluation questions will be scored, which comprise 7 factors, each scored on a scale of 0 to 3 points (0: no difficulty, 3: serious difficulty). The sum of all factor scores ranges from 0 to 21, with a total score of 21 indicating serious difficulty in all respects. The reference values for adult sleep quality problems in China are as follows: PSQI ≥8 indicates poor sleep quality, whereas PSQI ≤7 indicates good sleep quality; the higher the score, the worse the sleep quality.

##### Quality of Life Assessed Using the 36-Item Short Form Health Survey

The patients will be evaluated using the 36-item Short Form Health Survey (SF-36) at each observation point. The SF-36 is a general scale developed by the American Medical Research Group to evaluate the quality of life. It is widely recognized and used worldwide. This scale has 8 dimensions to evaluate health-related quality of life, which belong to 2 categories of physical health and mental health, namely physiological function, role-physical, bodily pain, general health, vitality, social function, role-emotional, and mental health. In addition, the SF-36 scale includes another indicator, health change, which is used to evaluate health changes over the past year.

### Secondary Outcome Measures

#### Insomnia Severity Index

The patients will be evaluated using the Insomnia Severity Index (ISI) at each observation point. The degree of insomnia is determined according to the total score: a score between 0 and 7 indicates no clinically significant insomnia, a score between 8 and 14 indicates subthreshold insomnia, a score between 15 and 21 indicates clinical insomnia (moderate to severe), and a score between 22 and 28 indicates clinical insomnia (severe).

#### 16-Item Dysfunctional Beliefs and Attitudes About Sleep Scale Score

The items in the 16-item Dysfunctional Beliefs and Attitudes About Sleep scale (DBAS-16) comprise 4 factors: potential consequences of insomnia, worry about sleep, sleep expectations, and cognition of insomnia drugs. The lower the total score, the more likely it is that the participants’ cognition of sleep is biased.

#### γ-Aminobutyric Acid

γ-Aminobutyric acid (GABA) is used as a secondary outcome indicator for insomnia treatment, mainly based on its physiological role as a central inhibitory neurotransmitter. Studies have shown that the hyperarousal state of patients with insomnia is closely related to a decrease in GABA levels in brain regions such as the anterior cingulate gyrus and occipital cortex, and GABA concentration is negatively correlated with objective sleep indicators (such as awake time during sleep). Magnetic resonance spectroscopy
can noninvasively and quantitatively determine the concentration of GABA in specific brain regions in vivo, thereby directly assessing whether the treatment improves sleep by enhancing the key mechanism of inhibitory neurotransmission.

#### Glutamic Acid

Glutamic acid (Glu) will be used as a secondary outcome indicator due to its key role in maintaining cortical excitability. Insomnia is often accompanied by excessive activation of the brain, which is related to abnormal activity of the glutamatergic system. Studies have shown that changes in the Glu levels in specific brain regions of patients with insomnia are associated with subjective sleep quality, anxiety, and anhedonia. Magnetic resonance spectroscopy can provide direct and quantitative information on Glu at the brain region level and thus will be used to verify whether the treatment restores the excitatory-inhibitory balance of the brain network by regulating excitatory neurotransmission.

### Indicators of Mechanism

#### Heart Rate Variability

The following HRV indices will be assessed: very LF (vLF), LF, HF, total power (TP), and LF/HF. Additionally, the parasympathetic nerve index (Log L×T) and sympathetic nerve index (Log L/T) will be calculated, where L denotes LF and T denotes TP, to evaluate ANS activity.

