A study that analyzed the effects of acupuncture on the ANS showed that acupuncture can reduce sympathetic nerve activity under stress conditions and balance the ANS [10]. In a review that included 14 studies on the effects of acupuncture on heart rate variability (HRV), it was reported that acupuncture can reduce the low-frequency power (LF) and the LF to high-frequency power (HF) ratio (LF/HF) in patients and may function to balance the sympathetic and parasympathetic nervous systems [11]. A previous study by the project leader found that acupuncture at the acupoints Tianrong (TE16) and Fengchi (GB20) can improve the autonomic nerve function of patients with migraine. Although studies have shown that acupuncture has a regulatory effect on autonomic nerves, there is still a lack of in-depth discussion on the mechanism [12]. At present, most studies on acupuncture treatment of insomnia do not strictly distinguish TCM syndromes, and it is difficult to accurately provide effective treatment options for specific syndromes. This study focuses on insomnia of liver depression and spleen deficiency type. It is expected to clarify the curative effect of acupuncture on insomnia of this type through rigorous randomized controlled trials (RCTs) and provide more targeted evidence for clinical treatment with TCM.

HRV reflects the functional status of sympathetic and parasympathetic nerves, which offers a window into the functional status of human ANS [13]. Therefore, it is believed that HRV reflects the mechanism of excessive arousal from the changes in autonomic nerve function, and improving HRV indices and reducing excessive arousal may be a new idea for the treatment of insomnia. We designed this study based on the theory of Jing Bie selection to explore the treatment of insomnia through the analysis of HRV.

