The selection of the cervical acupoints SI17 and TE16 is based on the classical meridian divergence (Jing Bie) theory of TCM [5]. According to “Lingshu · Jing Bie,” although SI17 belongs to the small intestine meridian, it is located at the intersection of the liver and gallbladder meridians. Therefore, acupuncture at SI17 can soothe and regulate the liver and gallbladder qi. Although TE16 belongs to the triple energizer meridian, it is located at the intersection of the triple energizer, pericardium, and gallbladder meridians. Acupuncture at TE16 can regulate the qi of the Shaoyang meridian, relieve the stagnation of the upper energizer and tranquilize the mind, and provide a theoretical basis for related diseases. In TCM, the neck is a key region where multiple yang meridians converge [18]. As pivotal acupoints in the neck, SI17 and TE16 are essential for regulating the mind and balancing yin and yang, and their clinical values stem from the deep regulation of ying-wei qi and blood by the hand Taiyang and hand Shaoyang meridians. Specifically, the Tianrong point follows the path of “entering the armpit and walking the heart” by the hand Taiyang meridian, which has the effect of dredging the neck qi and blood and calming the heart and nerves. Its anatomical deep layer corresponds to the cervical sympathetic ganglion, which can inhibit the excessive excitement of the sympathetic nerve. The Tianyou acupoint, with the function of the hand Shaoyang meridian “scattered in the chest,” can regulate the triple energizer qi, straighten out the upper energizer, and affect the activity of the vagus nerve. According to the “Lingshu · Jing Bie,” these divergences “branch from the main channels, enter the body cavity, link exterior and interior, and harmonize *ying* (nutritive) and *wei* (defensive) energies.” The yang meridians are different from the original meridians, and the yin meridians are different from the yang meridians in the exterior and interior, which strengthens the close relationship between the limbs and the zang-fu organs, head, and face. In TCM, insomnia of the liver depression and spleen deficiency type is considered to stem from disrupted qi flow and impaired balance between ying and wei [19,20]. The mechanism of acupuncture involves regulating the relationship between yin and yang, the unity of opposites, to restore the harmonious flow and balance of qi in the whole body [21]. On the basis of this principle, specific acupoints on the neck are stimulated to dredge the Shaoyang meridian and reconcile ying and wei so as to promote yang qi into yin and support natural sleep. This follows the classical TCM principle that “acupuncture treats areas along the pathway of the meridian.”

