### Proposed Mechanism and Empirical Testing

The proposed mechanism can be traced through specific physiological pathways. The anatomical proximity of these points to the cervical sympathetic chain means that stimulation may send signals through the spinal cord to higher brain regions that regulate autonomic function, such as the brain stem and hypothalamus [27,28]. This influence on the central nervous system can rebalance the sympathetic and parasympathetic activity, a change measurable through HRV [29-32]. Thus, HRV provides an objective link between the TCM idea of restored ying-wei harmony and modern metrics of ANS balance. Beyond this neural pathway, the intervention likely also involves neuroendocrine adjustments [33-35]. Chronic insomnia and the TCM pattern of liver qi stagnation are both associated with overactivity of the body’s stress response system, the hypothalamic-pituitary-adrenal axis [36-38]. By mitigating excessive sympathetic drive, acupuncture may help calm the hypothalamic-pituitary-adrenal axis hyperactivity [39], potentially leading to lower cortisol levels and a more sleep-conducive internal milieu [40-42]. In summary, the treatment is hypothesized to work through a convergent network, modulating both neural excitability and endocrine function to address the multifaceted pathophysiology of insomnia.

To empirically test this mechanistic model, our study employs a multimethod assessment strategy. In addition to standard patient-reported outcomes (PSQI and ISI), we will measure HRV to directly quantify ANS changes [43]. We will also analyze the levels of key neurotransmitters—GABA and Glu. We hypothesize that successful treatment will be correlated with a shift toward a less excited central nervous system state, reflected in an increased GABA to glutamate ratio [18]. This combined biochemical and physiological evidence aims to clarify how stimulation at these specific points translates into clinical improvement, thereby strengthening the scientific rationale for this targeted acupuncture protocol.

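### The HRV index labelled parasympathetic is defined as log(LF×TP), so it falls with LF, and by more than the index labelled sympathetic

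*Protocol article*

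**What the plan says.** The Heart Rate Variability section first lists the standard spectral measures: "The following HRV indices will be assessed: very LF (vLF), LF, HF, total power (TP), and LF/HF". It then adds two derived indices: "the parasympathetic nerve index (Log L×T) and sympathetic nerve index (Log L/T) will be calculated, where L denotes LF and T denotes TP". No other part of the article redefines L or T, and the section cites no source for the indices.

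Three other places show how HRV is to be read:

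- The Introduction cites a review reporting that "acupuncture can reduce the low-frequency power (LF) and the LF to high-frequency power (HF) ratio (LF/HF) in patients", and presents this as a possible balancing of the two branches.
- Study Rationale says of the tissue beneath one of the two test acupoints "which can inhibit the excessive excitement of the sympathetic nerve".
- Proposed Mechanism and Empirical Testing expects treatment to "rebalance the sympathetic and parasympathetic activity, a change measurable through HRV", and adds that "we will measure HRV to directly quantify ANS changes".

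Table 1 schedules HRV at weeks 0, 4 and 8 and classes it as an indicator of mechanism, neither primary nor secondary.

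**The concern.** An index named for a branch of the autonomic nervous system should move in the direction its name implies. Here LF multiplies total power in the parasympathetic index, so a fall in LF pulls that index down. The literature that the article relies on treats lower LF and lower LF/HF as the balancing pattern. HF, the other half of the LF/HF ratio, has no term of its own in either index.

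At stake is the reading of two mechanism results. Patients who show the cited pattern could be reported as having lost parasympathetic activity. The same values would enter the comparison with healthy controls, who are meant to supply reference values for HRV.

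**Working it through.** The article gives no figure to reproduce. The check is algebra on the stated definitions, followed by worked examples.

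**Inputs from the article (Heart Rate Variability section).** L = LF and T = TP. Parasympathetic index P = log(L×T). Sympathetic index S = log(L/T).

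**Assumptions.** TP = vLF + LF + HF, because the article does not define TP. Logs are base 10. All band powers below are illustrative and do not come from the article.

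**Step 1: expand.**
- P = log LF + log TP
- S = log LF − log TP

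**Step 2: response to each band, the others held fixed** (change in index per unit change in the log of the band).

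| Band | P | S |
|---|---|---|
| LF | 1 + LF/TP | 1 − LF/TP |
| HF | HF/TP | −HF/TP |
| vLF | vLF/TP | −vLF/TP |

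The LF coefficient lies between 1 and 2 for P and between 0 and 1 for S. So P always responds to LF more strongly than S does. HF and vLF have the same form. If TP is constant, the log TP terms cancel from any change, and P and S move by the same amount.

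**Step 3: examples from a base of vLF/LF/HF = 500/800/400 ms².** TP = 1700 and LF/HF = 2.0. P = log(800×1700) = 6.134. S = log(800/1700) = −0.327.

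| Change | TP | LF/HF | P (change) | S (change) |
|---|---|---|---|---|
| LF halved only | 1300 | 1.0 | log(400×1300) = 5.716 (−0.418) | log(400/1300) = −0.512 (−0.185) |
| LF halved, HF doubled | 1700 | 0.5 | log(400×1700) = 5.833 (−0.301) | log(400/1700) = −0.628 (−0.301) |
| HF +200 only | 1900 | 1.333 | log(800×1900) = 6.182 (+0.048) | log(800/1900) = −0.376 (−0.048) |
| vLF +200 only | 1900 | 2.0 | 6.182 (+0.048) | −0.376 (−0.048) |

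The last two rows are identical in P and S: the pair cannot tell a rise in HF from an equal rise in vLF.

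**Step 4: how far HF must rise to keep P unchanged after a 20% fall in LF.** P is unchanged when the new TP equals the old TP divided by 0.8.
- 500/800/400: new TP = 1700/0.8 = 2125, so HF = 2125 − 500 − 640 = 985, a rise of 146%.
- 300/300/300: new TP = 900/0.8 = 1125, so HF = 1125 − 300 − 240 = 585, a rise of 95%.
- 1000/500/500: new TP = 2000/0.8 = 2500, so HF = 2500 − 1000 − 400 = 1100, a rise of 120%.

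**Step 5: the other reading of the notation.** If Log L×T means (log L)×T, the index still rises with LF for any LF above 1, so the direction does not change.

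**The case against.** The strongest reply is that these two indices are extras. HF and LF/HF are listed ahead of them and would be reported beside them. In the second row of the examples, a reader would see HF double and LF/HF fall to 0.5. A reader might infer that the definition reverses the trial's mechanistic conclusion. The article does not support that, because the branch-relevant measures are also collected and are correctly labelled. This part of the reply stands.

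A reader might also infer that the pair cannot separate the two branches at all. That is too strong. P and S are different combinations of LF and TP, and both quantities can be recovered from them. A change in HF alone moves P up and S down, as the labels imply. Equal movement occurs only when TP is constant, and the second example was chosen with TP at 1700 throughout. Nor is the fall in P unconditional: a large enough rise in HF or vLF offsets it.

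Finally, the article sets no directional LF hypothesis for this trial. The Introduction reports a review's finding in cautious terms, and the mechanism section speaks only of rebalancing. The expected direction is an inference, though the Study Rationale's expectation of sympathetic inhibition lends it some support.

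None of this reconciles the formula with its label. The symbols are fixed explicitly in the text, so the matter is not a detail left to a fuller document. A reader might guess what L and T were originally meant to denote, but the article offers nothing on that and the point does not depend on it.

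**Conclusion.** The point holds for the two derived indices only. As defined, the index labelled parasympathetic falls when LF falls with the other bands fixed, and always by more than the index labelled sympathetic. The pattern cited as balancing would usually register as a parasympathetic loss. To avoid that after a 20% LF fall with vLF unchanged, HF would have to rise by more than about 95% to 146% across the three assumed spectra.

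The direction follows from the stated formulas together with TP = vLF + LF + HF. The sizes rest on assumed band powers. HRV is exploratory here, so this is a definite but contained error, worth correcting before analysis.

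**What to change.** Before any HRV analysis, trace the two indices to their source, establish what L and T denote there, and correct the definition so that each formula fits its label. If that cannot be done, or the quantities needed were not kept, delete both indices and base statements about the two branches on HF and LF/HF, which the section already lists. In either case, state how TP is formed.

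This needs no extra visits, measurements or participants, and recruitment is still under way. The article does not say which HRV data are stored, so it is uncertain whether a corrected index can be computed for patients already assessed. The downside is that two supplementary indices may be lost.

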#### Polysomnography

The participants will be monitored by polysomnography at the TCM Diagnosis and Treatment Center of Sleep Disorders in the Department of Acupuncture and Moxibustion of our hospital after 4 weeks of treatment and at 4 weeks after the treatment ends. The monitoring was performed using a Philips polysomnography system (model: Alice 6). Positioning and interpretation will be performed according to Berry et al [15]. The changes in the sleep parameters of patients will be analyzed using the data collected by Sleepware G3 (Philips Respironics), including sleep efficiency, the proportion of each sleep stage, sleep latency, and other sleep indicators corresponding to other stages.

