**Figure 1. F1:**
[figure not shown]
Study flowchart. DBAS-16: 16-item Dysfunctional Beliefs and Attitudes About Sleep scale, GABA: γ-aminobutyric acid, Glu: glutamic acid; HRV: heart rate variability; ISI: Insomnia Severity Index; MRI: magnetic resonance imaging; PSG: polysomnography; PSQI: Pittsburgh Sleep Quality Index; SF-36: 36-item Short Form Health Survey.

**Table 1. T1:** Schedule of study assessments and outcome measures.

Research stage	Before treatment	Treatment stage	Follow-up stage
Assessment	First	Second	Third
Time (weeks)	0	4	8
Informed consent	✓	—^a^	—
Inclusion/exclusion criteria	✓	—	—
Demographic data	✓	—	—
Vital signs	✓	—	—
Medical history record	✓	—	—
Physical examination	✓	—	—
Medication situation	✓	—	—
Indicator of mechanism			
HRV^b^	✓	✓	✓
PSG^c^	✓	✓	✓
MRI^d^	✓	✓	—
Primary outcome indicator			
PSQI^e^	✓	✓	✓
SF-36^f^	✓	✓	✓
Secondary outcome indicator			
ISI^g^	✓	✓	✓
DBAS-16^h^	✓	✓	✓
GABA^i^	✓	✓	—
Glu^j^	✓	✓	—
Safety evaluation	✓	✓	✓

a Not applicable.

b HRV: heart rate variability.

c PSG: polysomnography.

d MRI: magnetic resonance imaging.

e PSQI: Pittsburgh Sleep Quality Index.

f SF-36: 36-item Short Form Health Survey.

g ISI: Insomnia Severity Index.

h DBAS-16: 16-item Dysfunctional Beliefs and Attitudes About Sleep scale.

i GABA: γ-aminobutyric acid.

j Glu: glutamic acid.

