**Exclusion criteria (patients who meet any one of the following criteria will be excluded)**
Patients with insomnia caused by a variety of organic diseases or neurological or psychiatric disordersPregnant or lactating patients or those with a drug allergyPatients with more serious primary diseases such as cardiovascular and cerebrovascular diseases, gastrointestinal diseases, endocrine system diseases, or psychiatric disordersPatients with coagulation dysfunction and bleeding tendency

The baseline assessment will be performed by the same physician, and the results will be recorded in detail in the case report form. All participants will receive treatment for 4 weeks and undergo follow-up observation after treatment. The evaluation will be done at 3 time points: before treatment, after 4 weeks of treatment, and at 4 weeks after end of treatment. Each participant will receive a schedule of treatment dates and a schedule of follow-up appointments developed by research assistants who will be blinded to the grouping information.

In addition, all participants will be required to keep a sleep diary throughout the treatment and follow-up periods, recording the date of each insomnia episode, the length of time required to fall asleep, the number of times they wake up at night, the difficulty of falling asleep again, and the subjective feelings after waking up in the morning. Moreover, they will be asked to include sleep-related details as well as the name, dose, and time of use of other drugs (such as sleeping pills) during the trial and their own feelings after taking the drug.

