### Sample Size and Statistical Methods

The main outcome measure of this study will be the total PSQI score at 4 weeks after treatment. The sample size was calculated on the basis of the expected difference between the test acupuncture group and the conventional acupuncture group in this index.

The expected effect size was determined as follows: studies have shown that acupuncture can significantly reduce PSQI scores compared with conventional therapy, with a combined mean difference of 2.0 to 3.5 points [16]. With reference to an RCT of similar design [17], we conservatively estimated that the mean difference (Δ) of PSQI between the 2 groups after treatment was 2.5 points, and the combined SD was approximately 4.0 points. According to this calculation, the standardized effect size is 0.625 (Δ/SD=2.5/4.0). Using G*Power software (version 3.1; Heinrich-Heine University Dusseldorf), setting α=.05 (bilateral) and test efficiency (1-β)=80%, according to a 1:1 distribution, the minimum sample size of each group was calculated to be 43. Considering a dropout rate of approximately 10%, 48 patients will be included in each group, and a total sample size of 96 patients was finally determined.

SPSS software (version 22.0; IBM Corp) will be used to analyze the collected data. All data will be expressed as mean (SD). For measurement data of the 2 groups, normally distributed data will be analyzed by independent 2-tailed *t* test and paired 2-tailed *t* test. If the data are not normally distributed, the Mann-Whitney rank sum test will be used. One-way ANOVA will be used for comparison between groups. Count data will be analyzed using a chi-square test, and rank data will be compared using the rank sum test and other analysis methods. A *P* value of ≤.05 will be considered statistically significant. To control for potential confounding, the use of concomitant medications and measures derived from sleep diaries will be incorporated as covariates into a generalized linear model for sensitivity analysis of the primary outcomes.

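### The polysomnography section names recordings at weeks 4 and 8 but none before treatment, in conflict with Table 1, which also schedules week 0

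*Protocol article*

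**What the plan says.** The timing of polysomnography is given in two places, and they differ.

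- **Polysomnography (Indicators of Mechanism).** Recordings are made "after 4 weeks of treatment and at 4 weeks after the treatment ends". No pre-treatment recording is mentioned. The section goes on: "The changes in the sleep parameters of patients will be analyzed".
- **Table 1.** The time row reads "Time (weeks) 0 4 8", and the polysomnography row is ticked in all three columns.

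Two other places bear on the reading. The text after the exclusion criteria gives the trial's general evaluation points as "before treatment, after 4 weeks of treatment, and at 4 weeks after end of treatment". Sample Size and Statistical Methods names, for measurement data, the "independent 2-tailed *t* test and paired 2-tailed *t* test", with rank-based and ANOVA alternatives. The only covariate model there is a sensitivity analysis of the primary outcomes, using concomitant medication and sleep-diary measures. Polysomnography is classed as an indicator of mechanism, neither a primary nor a secondary outcome.

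**The concern.** The Polysomnography section does not fit its own stated purpose. It intends to analyse changes in sleep parameters, yet on the timing it gives, both recordings fall after treatment has ended. The one change available would run from week 4 to week 8. That describes whether an effect persists after treatment, not what treatment did. The paired t test would have no pre-treatment value to pair with.

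Polysomnography is the trial's only objective sleep measure: PSQI, ISI and the diary are self-reported, HRV is autonomic, and the spectroscopy is neurochemical. Timing matters because a pre-treatment recording that was not made cannot be made later. Recruitment began in January 2024 and 40 participants had been enrolled by December 2025. The contradiction may therefore already have affected some patients, while most of the sample is still to come.

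**Working it through.** **1. The two schedules side by side.**

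| Source | Week 0 | Week 4 | Week 8 |
|---|---|---|---|
| Polysomnography section | not named | yes | yes |
| Table 1, polysomnography row | yes | yes | yes |
| General evaluation points (all assessments) | yes | yes | yes |

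The section gives two recordings and Table 1 gives three. The difference is the pre-treatment one.

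**2. What each schedule allows.**

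| Analysis | Weeks 4 and 8 only | Weeks 0, 4 and 8 |
|---|---|---|
| Change from baseline | not possible | possible |
| Paired before-after test within an arm | not possible | possible |
| Change from week 4 to week 8 | possible | possible |
| Between-arm comparison at week 4 or 8, unadjusted | possible and valid | possible and valid |
| Between-arm comparison adjusted for baseline | not possible | possible |

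**3. Whether the sample size is touched.** It rests on the PSQI alone: difference 2.5, SD 4.0, standardised effect 2.5/4.0 = 0.625, two-sided α of .05, 80% power. The exact two-sample t calculation gives 41.17, so 42 per group. The stated 43 is close to this and has 81.7% power. Allowing 10% dropout, 43/(1 − 0.10) = 47.8, rounded up to 48, as stated. No polysomnography quantity enters, so the point leaves this calculation unchanged.

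**4. What a week-0 value could add (illustration).** The article gives no correlation between baseline and later polysomnography values, so r is assumed. For a between-arm comparison, the variance of the unadjusted estimate relative to the baseline-adjusted one is about 1/(1 − r²).

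- r = 0.3: 1/(1 − 0.09) = 1.10, or 10% more variance
- r = 0.5: 1/(1 − 0.25) = 1.33, or 33% more
- r = 0.6: 1/(1 − 0.36) = 1.56, or 56% more

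**5. How many patients can still be covered.** Even if all 40 enrolled participants were patients, 96 − 40 = 56 patients remained to be enrolled as of December 2025.

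**The case against.** The strongest reply is that the baseline recording is already specified. The study design section points to Table 1 as the schedule of assessments, and Table 1 ticks week 0. The general evaluation points include one before treatment, and the Polysomnography section's own reference to changes presupposes a baseline. On this reading a phrase dropped out of one sentence. That is the likely explanation, and it means that the design as scheduled is sound. It does not remove the contradiction: the article states the timing twice, differently, and the section describing how the recordings are made is the one lacking the baseline.

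A reader might infer four stronger things, none of which the document supports.

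- *That a baseline recording is ruled out, or that the sleep laboratory works from this section.* The section lists two times without excluding a third, and nothing gives it precedence over Table 1.
- *That no change at all could be computed.* The week 4 to week 8 change would remain. What would be lost is change from baseline.
- *That a between-arm result could not be trusted without a baseline.* Randomisation keeps the comparison at weeks 4 and 8 unbiased in expectation, and the test's error rate already allows for chance imbalance.
- *That the stated plan would lose 10% to 56% in precision.* The plan names no baseline-adjusted analysis of polysomnography, so its between-arm t test loses nothing of that kind.

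It can also be said that the choice of an adjusted analysis is commonly left to the statistical analysis plan, which is not shown. That is fair. Its absence here is not a defect, and the adjustment is offered as an improvement.

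**Conclusion.** The contradiction is real and sits in current text. Its consequence is conditional. If the Polysomnography section were followed instead of Table 1, change from baseline and the paired before-after comparison would be lost for every patient so handled, without remedy. The randomised comparisons at weeks 4 and 8 would stand, though without the option of baseline adjustment.

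The reach is limited to one mechanism indicator. The primary outcome is outside it. The point still deserves correction now, because it governs whether a recording is made at all and enrolment is under way. The document does not show whether any enrolled patient lacks a week-0 recording, and no such loss is asserted here. The variance range depends entirely on the assumed correlations of 0.3 to 0.6, and the conclusion does not rest on it.

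**What to change.** 1. In the Polysomnography section, add a recording before treatment (week 0) to the two already named, so that it agrees with Table 1.
2. Confirm which patients already enrolled have a week-0 recording, and report that number by arm.
3. Compare the arms at weeks 4 and 8 adjusted for the week-0 value, for example by analysis of covariance, for the patients who have one.

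The first change is one sentence and adds no procedure, since Table 1 already schedules the recording. The second is a check of existing records. The third uses data that the trial already plans to collect.
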